**Progression criteria**

Progression criteria for recruitment is:

- Green (progress to full trial). At least 80% of target recruited (n ≥ 36)
- Amber (full trial considered feasible if reasons for poor recruitment identified and can be addressed). Between 40% and <80% of target recruited (n between 18 and 35, inclusive)
- Red (unlikely to progress to full trial. Substantial amendments will be necessary to make a full trial feasible). Below 40% of target recruited (n<18).

**Objective 2.** What is the level of engagement with adherence to the iMAPS-2 intervention (therapy sessions attendance measures; therapist fidelity)?

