## Trial Design

24-month feasibility randomised controlled trial comparing treatment as usual plus iMAPS therapy, versus treatment as usual, with a 2:1 allocation ratio. The study is funded by the UK National Institute for Health Research as part of a rapid call for Mental Health projects in the North of England to be conducted within 24 months. The study therefore has a nine-month recruitment window to recruit 45 participants. As this is a feasibility study, we aim to find out from service users/participants who are allocated to receive the iMAPS therapy about their experiences of taking part in the trial, receiving the therapy and suggestions for improvements. Therefore, our study design ensures that most of our service users in the study will be allocated to iMAPS therapy by using a 2:1 allocation.

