## Study Setting

**Setting:** NHS Early Intervention (EI) in Psychosis and Community Mental Health Team services, including inpatient wards Pennine Care NHS Foundation Trust (Greater Manchester). Forty-five participants will be recruited in Pennine Care NHS FT (30 in the iMAPS plus usual care arm and 15 in the usual care arm). The recruitment rate will be five participants per month, for approximately nine months.

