**Full Trial Progression Criteria:**

We will progress to a full trial if we all our criteria below are classed as GREEN; if one or more is AMBER, we will investigate whether it is possible to make adjustments to the trial design to overcome any problems and, if that appears possible, progress to a full trial (including an assessment of the success of our adjustments in its internal pilot, where appropriate); if one or more is RED, we will not progress unless we can make the substantial amendments which would be necessary to make a full trial feasible.

1. Recruitment: GREEN: >=80% (n>=36) of target recruited; AMBER >=40 % (n=18-35)-< 80% of target recruited; RED <40% (n<18) of target recruited.
2. Retention: GREEN: >=80% of participants providing 16-week outcome data ; AMBER: >60%- <80% of

participants providing 16-week outcome data; RED: <60% of participants providing 16-week outcome data.

- 1. Adherence: GREEN>=75% adherence of participants attend at least 5 sessions of therapy, AMBER>=40% participants

attend at least 5 sessions of therapy; RED: <40% of participants attend at least 5 sessions of therapy (based on Jolley et al. 2015).

Assessment Measures

|  | **Procedures and Questionnaires** | **Mins** | **Baseline** | **16 Weeks Follow Up** | **28 Weeks Follow Up** |
| --- | --- | --- | --- | --- | --- |
|  | Demographics | 5 | X | As needed | As needed |
| **Psychosis Measures** | PANSS | 60 | X | X | X |
|  | PSYRATS | 15 | X | X | X |
|  | QPR | 5 | X | X | X |
| **Imagery** | Brief Imagery Interview  Visual Analogue Scales/MIPQ  Psychosis Imagery Questionnaire (PIQ) | 10  5 | X  X | X | X |
| **Schemas** | BCSS | 2 | X | X | X |
| **Trauma** | TALE | 5 | X |  |  |
|  | ITQ | 5 | X | X | X |
|  | BES | 5 | X | X | X |
| **Mental Health and Functioning** | BAI | 5 | X | X | X |
|  | CDS | 9 | X | X | X |
|  | WEMWBS | 5 | X | X | X |
|  | PSP | 10 | X | X | X |
| **Health Economics** | EQ-5D-5L | 2 | X | X | X |
|  | ReQoL-10 | 2 | X | X | X |
|  | Economic Patient Questionnaire | 10 | X | X | X |
|  |  |  |  |  |  |
| **Working Alliance** | WAI-client | 5 | 3^rd^ Session | 6^th^ | 9^th^ |
|  |  | 5 |  |  |  |
| **THERAPIST ONLY** | WAI-therapist | 5 | 3^rd^ Session | 6^th^ | 9^th^ |
|  | iMAPS therapy fidelity Checklist  CTS-R or CTS-Psy |  | A selection of therapy sessions will rated in supervision and by an independent external therapist |  |  |
| **Adverse Effects** | CGI-IP | 1 | Each Session |  |  |
|  | CGI-SP | 1 | Each Session |  |  |

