## Sample Size

As this is a feasibility trial, it is not powered to detect between-group differences. But we will seek to estimate recruitment and retention parameters as well as the SD in outcome measures with reasonably good precision. Recruiting 45 participants will allow us to estimate the retention rate at end of therapy via a 95% (exact binomial) confidence interval, with width no greater than 25%, assuming retention is at least 80%.  It will also suffice for the estimation of the SD, although the sample size (expected minimum 36 participants with outcome data) is towards the lower end of the sample size recommended (Julious, 2005; Sim and Lewis, 2012).  This is a recruitment rate average of five participants per month over nine months (with 2.0 WTE Research Assistants). The study will not be powered to detect between-group differences, however, the study will test participants willingness to be randomised to an imagery focused therapy trial with a control arm. But we will seek to estimate recruitment and retention parameters as well as the variance in outcome measures and the sample size will suffice to meet these and other project objectives.

In the participant’s qualitative study, we will seek to recruit 15-20 participants to take part in qualitative interview about their experiences of participating. In the clinicians/referrers interviews, we will seek to recruit 10 referrers to talk about their experience of referring to the trial. The participants will receive £15 as a token of thanks for taking part in the interviews.

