**Analysis**

The number of people screened, eligible, consented and randomised will be summarised and reported in a CONSORT flow diagram (see section 6).

Randomisation rates to assess the progression criteria to conduct a definitive trial will be presented as point estimates with (exact binomial) 95% confidence intervals.

Monthly randomisation rates will also be presented overall and tabulated by randomised group as stated in section 6.3

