**Additional Tables**

**Monthly and cumulative randomisation**

We were interested in the number and percentage of eligible patients/service users consenting to the trial (recruitment).

Participant recruitment began on 14^th^ July 2022 and the final participant was randomised on 08^th^ September 2023. The study recruited its target of 45 participants randomised, 100%, 95%CI (92% to 100%) and therefore met the green criteria for recruitment. Monthly and cumulative randomised figures are shown in the table below. The overall average monthly rate randomised was 45/15 = 3 participants per month.

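### The recruitment progression criterion has no time limit, and its binomial interval on 45/45 says nothing about recruitment

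*Combined protocol and SAP*

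**What the plan says.** **The plan has a clock.** Protocol, Trial Design: "The study therefore has a nine-month recruitment window to recruit 45 participants". Study Setting: "The recruitment rate will be five participants per month, for approximately nine months". Sample Size repeats the pace: "This is a recruitment rate average of five participants per month over nine months".

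**The criterion has none.** Protocol, Full Trial Progression Criteria: "Recruitment: GREEN: >=80% (n>=36) of target recruited". SHEAP 7.2, Objective 1, gives the same GREEN threshold, "Green (progress to full trial). At least 80% of target recruited (n ≥ 36", and AMBER as "Between 40% and <80% of target recruited (n between 18 and 35, inclusive". RED is below 18. No period is attached to any class in either document. SHEAP 6.3 and 7.2 also plan monthly randomisation figures, but set no threshold for them.

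**The interval.** SHEAP 7.2, Objective 1, Analysis: "Randomisation rates to assess the progression criteria to conduct a definitive trial will be presented as point estimates with (exact binomial) 95% confidence intervals". Protocol, Analysis Methods, likewise names exact binomial methods for recruitment rates.

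**The result.** Additional Tables, Monthly and cumulative randomisation: "The study recruited its target of 45 participants randomised, 100%, 95%CI (92% to 100%) and therefore met the green criteria for recruitment". The same paragraph dates recruitment from 14 July 2022 to 8 September 2023 and gives an average of 3 per month. Supplementary Table 12 records that the recruitment window was extended, with reasons.

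**The concern.** A count with no period cannot separate a trial that fills in nine months from one that fills in fourteen. If the window can be extended until the target is met, GREEN depends on how long the team can keep recruiting and not on pace. Pace is what a definitive trial's timetable and budget rest on.

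The interval adds apparent precision without content. An exact binomial interval describes a fixed number of independent trials, each of which could fail. Here recruitment ended when the 45th participant was randomised, so the numerator equals the denominator by design. The 92% lower limit reflects only the size of the target.

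At stake is one of the three progression classes. AMBER asks the team to identify the reasons for poor recruitment and show that they can be addressed. GREEN does not.

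**Working it through.** **1. Reproduce the reported interval.** For x = n = 45 the exact (Clopper-Pearson) lower limit is 0.025^(1/45) = 0.921 and the upper limit is 1. This matches the reported 92% to 100%. The formula contains no time, so every trial that fills a target of 45 obtains it.

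**2. Count at nine months.** Running totals from Supplementary Table 1:

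| Month end | Randomised in month | Cumulative | % of 45 |
|---|---|---|---|
| Nov 2022 | 5 | 8 | 18 |
| Dec 2022 | 3 | 11 | 24 |
| Jan 2023 | 4 | 15 | 33 |
| Feb 2023 | 6 | 21 | 47 |
| Mar 2023 | 3 | 24 | 53 |
| Apr 2023 | 5 | 29 | 64 |
| May 2023 | 5 | 34 | 76 |
| Jun 2023 | 3 | 37 | 82 |
| Jul 2023 | 1 | 38 | 84 |
| Aug 2023 | 3 | 41 | 91 |
| Sep 2023 | 4 | 45 | 100 |

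Nine months from 14 July 2022 end on 14 April 2023. The table is by calendar month, so the count lies between 24 (end March) and 29 (end April): 24/45 = 53% to 29/45 = 64%. The whole range falls in AMBER (18 to 35). The GREEN count of 36 was reached in June 2023 (34 at end May, 37 at end June).

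**3. Sensitivity to the start of the clock.** Starting at the first randomisation (August 2022), nine months end between end April and end May 2023, with 29 to 34 randomised (64% to 76%): still AMBER. Of the runs of nine calendar months in the table, only October 2022 to June 2023 reaches 36 (37 − 1 = 36), and the documents give no reason to start there.

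**4. Rate.** 14 July 2022 to 8 September 2023 is 421 days; 421/30.4375 = 13.8 months. Exact Poisson 95% limits for 45 events are 32.8 and 60.2.

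- Elapsed time: 45/13.83 = 3.25 per month (32.8/13.83 = 2.4 to 60.2/13.83 = 4.4).
- The document's 15 calendar months: 45/15 = 3.0 per month (32.8/15 = 2.2 to 60.2/15 = 4.0).

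These are 65% and 60% of the planned five per month, and both intervals exclude five. The rate matching GREEN is 36/9 = 4.0 per month; neither interval clearly excludes that (upper limits 4.35 and 4.01).

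**5. Effect on a timetable.** A plan at five per month allows nine months for 45. Against the time taken, the understatement is 1 − 9/13.83 = 35%, or 1 − 9/15 = 40%.

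**The case against.** **GREEN was correctly awarded.** Both documents set the rule as a count, and 45 exceeds 36. A reader might infer that the result should be restated as AMBER. The documents do not support that: replacing a pre-specified threshold once all the counts are known would itself be post hoc. The fault lies in the rule, not in how it was applied. This stands.

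**Nothing is concealed.** A reader might infer that slow recruitment was hidden. It was not. The average of 3 per month follows in the same paragraph as the GREEN statement, every month is tabulated, and Supplementary Table 12 gives the extension and its reasons: research assistants leaving, investigator leave and clinical-team absences. This also stands. What remains is that none of it enters the decision rule.

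**The label may not change the decision.** AMBER permits progression after adjustment, and reasons have already been named. Whether they can be addressed is not shown. This lowers the severity but does not remove the defect.

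**Binomial intervals have a place in Objective 1.** Its question is what share of eligible patients consent, and SHEAP 5.3 plans such proportions. For those the method is sound. The objection fails only for n/45, which is how the interval was in fact used.

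**Poisson does not match a stopping count exactly.** If 45 is fixed, time is the random quantity and a gamma interval is the strict choice. It gives 2.37 to 4.27 per month over 13.83 months, against 2.37 to 4.35 for Poisson. Both exclude five.

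**Passing at any speed is too strong a reading.** The study was funded for 24 months and has a 28-week follow-up, which limits how long recruitment can run, although the end date was extended.

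**Conclusion.** The criterion omits the period on which the recruitment plan depends, and the interval attached to it is invalid for a target that ended recruitment. Followed as written, the plan returns GREEN with 100% (92% to 100%) at about 60% to 65% of the intended pace. At nine months from opening the count was 24 to 29 of 45, in the AMBER range. A timetable built on five per month would be about 35% to 40% too short.

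This rests on the clock starting at the stated opening date and on the monthly table being complete (it sums to 45). The AMBER range also holds if the clock starts at the first randomisation. The point does not show that recruitment failed or that a full trial is infeasible, and the rate intervals reach 4.0 per month. It should be fixed, but it is not a barrier to progression.

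**What to change.** 1. Delete the binomial interval on n/45. Report the monthly rate with an exact Poisson 95% interval, or the near-identical gamma interval, and state the time base. Keep binomial intervals for consent and randomisation among eligible patients.
2. Keep GREEN as the pre-specified verdict. Beside it, labelled post hoc, report 24 to 29 of 45 at nine months (AMBER range; the exact figure follows from the randomisation dates) and the extended window.
3. Report there too the widening of eligibility to age 16 and inpatient wards, dated 21 November 2022 in Supplementary Table 12. Only 8 of 45 had been randomised by the end of that month, so 45 − 8 = 37 came later. The CONSORT checklist (Supplementary Table 11) marks changes to methods after commencement as not applicable and should agree with this.
4. State the period in the criterion: randomised within nine months of opening, GREEN at least 36, AMBER 18 to 35, RED below 18. Change protocol and SHEAP together, since editing one alone would create a contradiction, or put the period into the definitive trial's internal-pilot criteria.

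The cost is a few lines of text and one recalculation from published counts. The downside is a less favourable recruitment result, although AMBER would still allow progression if the reasons are identified and can be addressed.

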**Outcome**

Participant adherence

- Number of sessions of iMAPS-2 therapy attended for those participants allocated to the intervention arm.

Therapist fidelity:

- The Cognitive Therapy Rating Scale Revised (CTS-R) or
- The Cognitive Therapy Rating Scale for Psychosis (CTS-Psy)
- Therapist checklist.

**Analysis**

Assessment of participant’s adherence and therapist fidelity are fully described in section 5.2.1.

The proportion of participants allocated to the intervention arm, attending at least 5 sessions of the iMAPS-2 therapy will be presented as point estimates with 95% (exact binomial) confidence intervals to assess the progression criteria to conduct a definitive trial.

In addition, we will report the proportion of participants whom have received at least 5 hours (300 minutes) of the iMAPS-2 therapy along with a 95% (exact binomial) CI. We will also summarise, as mean(SD) or median(IQR) as appropriate, the overall hours of iMAPS-2 therapy received, and the hours of iMAPS-2 therapy received by the adherent participants (those who received at least 5 sessions).

Finally, we will plot:

- A histogram showing the distribution of iMAPS-2 therapy sessions attended (whether they are part or whole sessions).
- A histogram showing the distribution of hours of iMAPS-2 therapy sessions attended.

**Progression criteria**

Progression criteria for participant adherence is:

- Green (progress to full trial). At least 75% of the participants allocated to the intervention arm attend at least 5 sessions of iMAPS-2 therapy.
- Amber (full trial considered feasible if reasons for poor participant’s adherence identified and can be addressed). 40% - <75% of the participants allocated to the intervention arm attend at least 5 sessions of iMAPS-2 therapy.
- Red (unlikely to progress to full trial. Substantial amendments will be necessary to make a full trial feasible). If less than 40% of the participants allocated to the intervention arm attend at least 5 sessions of iMAPS-2 therapy.

**Objective 3.** What completion and data quality rates can be achieved (data completion and retention of participants)?

**Outcome**

- Number of participants continuing in the trial at 16 weeks.
- Number of participants completing the trial at 28 weeks.
- Questionnaire completion rates (after missing item imputation) at baseline, 16 weeks and 28 weeks for the following instruments:
  - Positive and Negative Syndrome Scale (PANSS)
  - Psychotic Symptom Rating Scales (PSYRATS)
  - Questionnaire about the Process of Recovery (QPR)
  - Mental Imagery in Psychosis Questionnaire/Visual Analogue Scales Visual Analogue Scales (MIPQ)
  - Brief Core Schema Scale (BCSS)
- Number of completed items per questionnaire as listed in the previous bullet point and prior to missing item imputation.

**Analysis**

The number of participants attending each of the 16- and 28-week trial visits will be summarised and reported in a CONSORT flow diagram (see section 6.3). In addition, retention rates at 16 weeks to assess the progression criteria to conduct a definitive trial, and also at 28 weeks, will be presented as point estimates with 95% (exact binomial) confidence intervals.

We will summarise the frequency (%, with denominator the number attending the corresponding visit) of the completed instruments (after missing item imputation) listed above by time point. We will also report the number of completed items per instrument (prior to missing item imputation) at each time point, and frequency (%) of valid scale (and subscale) scores for each instrument.

If any of the candidate primary outcome measures shows a significant amount of missing item data (more than 5% of partially or fully completed questionnaires), we will present the % of missing data by item to identify problematic items or sets of items.

**Progression criteria**

Progression Criteria for retention (baseline to primary outcome completion at 16-weeks) is:

- Green (progress to full trial). At least 80% retention:
- Amber (full trial considered feasible if reasons for poor retention identified and can be addressed). 60%-<80% retention
- Red (unlikely to progress to full trial. Substantial amendments will be necessary to make a full trial feasible). Below 60% retention.

**Objective 4.** What estimates of effect sizes (if any) are present (acknowledging this is a feasibility trial)?

**Analysis**

We shall analyse each of the candidate primary outcomes (i.e., Positive and Negative Syndrome Scale (PANSS) Total score, Psychotic Symptom Rating Scales (PSYRATS), Questionnaire about the Process of Recovery (QPR) and Brief Core Schema Scale (BCSS), using a separate linear regression model at each time-point to estimate the effect sizes at 16 and 28 weeks.

Each model will be fitted to the clinical outcome measure at the respective assessment time-point (16 or 28 weeks) and will include the fixed-effects for treatment therapy (iMAPS-2+TAU or TAU), care team type (CMHT or EI) and the corresponding baseline outcome score.

Models will be fitted using Maximum Likelihood Estimation (MLE).

Point estimates will be presented as regression coefficients and a range of confidence intervals at different confidence levels (75%, 80%, 85%, 90% & 95%) will be structured and examined as whether they are likely to capture the minimal clinically important difference (MID) for the primary end-point (i.e., 16 weeks). Point estimates with 95% confidence intervals will be presented at 28 weeks.

For this purpose, the MID will, in general, be a SES of 0.3, and so the confidence intervals used for comparison with the MID will likewise be standardised using the overall baseline SD. However, for the PANSS Total Score, the confidence intervals for the effect estimates on the unstandardised scale will also be compared with the proposed MID of 5 points.

These analyses will be used to consider evidence as to potential proof of effectiveness and will also provide estimates of their SD to assist with the estimation of the required sample size for a full effectiveness trial (Objective 6), should that measure be retained for consideration as primary. We will report the estimated standardised effect size (SES)= Effect estimate / SD_pooled_ with their corresponding 95%CIs calculated dividing the limits of the 95%CI of the effect estimate by the SD_pooled_.

The remaining continuous outcomes listed in section 7.1 will be analysed in the same fashion than the candidate primate outcomes. Each regression model will be fitted to the clinical outcome measure at the respective assessment time-point (16 or 28 weeks) and will include the fixed-effects for treatment therapy (iMAPS-2+TAU or TAU), care team type (CMHT or EI) and the corresponding baseline outcome score. Estimates of the treatment effects will be presented as the mean difference with 95% CIs.

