## Sample size

Recruiting 45 participants will allow to estimate the retention rate at end of therapy with a 95% (exact binomial) confidence interval (CI), with width no greater than 25%, assuming retention is at least 80%.  It will also suffice for the estimation of the SD, although the sample size (expected minimum 36 participants with outcome data) is towards the lower end of the sample size recommended [1] [2]

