# Statistical Principles

## Confidence intervals (CI) and level of statistical significance

As this is a feasibility study, the emphasis will be on producing relevant data summaries.. For consideration of potential proof-of-efficacy investigations (i.e., Positive and Negative Syndrome Scale (PANSS) Total score, Psychotic Symptom Rating Scales (PSYRATS), Questionnaire about the Process of Recovery (QPR) and Brief Core Schema Scale (BCSS)), two-sided 100*(1-α)% confidence intervals with α ranging from 0.05 to 0.25 (in steps of 0.05) will be computed [3], thus reporting adjusted point estimates and confidence intervals (CIs), ranging from 75% to 95% confidence, for the effect obtained from the analyses described in section 7.2. This approach is based on a minimally-important difference (MID) between trial arms and is therefore more appropriate than formal hypothesis testing when a study is underpowered.

The MID for the PANSS total score can range between 4 and 21 points [4] [5]. Due to lack of literature to select appropriate MID for the PANSS and the rest primary outcome candidates, we define a promising effect to be around a standard effect size of 0.3 (or more) [ref]. In addition, we will consider an absolute change of 5 points in the Total PANSS scores as a promising effect.

Two-sided 95% confidence intervals will be presented for the estimates of the treatment effects of all other continuous outcomes. No formal testing will be performed and, as a result, p-values will not be presented.

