***Regression diagnostics***

Diagnostic checks to assess the appropriateness of the regression models fitted will be through the use of residual plots. We will plot:

- Histograms and probability plots of the residuals to assess normality
- Scatter plots of residuals against fitted values to assess constant variance and linearity, and to identify potential outliers.

Should the normality assumption be untenable for the continuous outcomes, bootstrap methods will be applied to estimate the confidence intervals of the treatment effects.

**Objective 6.** What is the estimated sample size for a fully powered trial to evaluate the effectiveness of iMAPS-2 (relative to usual care)?

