|  | Median(IQR) | 13.5 (7.0 to 17.0) | 16.0 (12.0 to 19.0) | 14.0 (12.0 to 17.0) | 0.0 (0.0 to 12.0) | 12.0 (5.0 to 20.0) | 5.0 (0.0 to 12.0) |
|  | Missing | 0 | 0 | 0 | 1 | 0 | 1 |

**Supplementary Table 4d: Post Hoc Analysis Treatment effects at 16 weeks of the Psychotic Symptom Rating Scales (PSYRATS) for those participants with auditory hallucinations & delusions at baseline**

|  | **Scale range** | **N** | **Effect estimate** | **in favour of …** | **95% CI** | **90% CI** | **85% CI** | **80% CI** | **75% CI** | **SD_pooled_** | **SES (95%CI)** |
| --- | --- | --- | --- | --- | --- | --- | --- | --- | --- | --- | --- |
| **Psychotic Symptom Rating Scales (PSYRATS)** | |  |  |  |  |  |  |  |  |  |  |
| Auditory Hallucinations Subscale (AHS) | 0-44 | 17 | -3.4 | iMAPs | (-17.4 to 10.6) | (-15.1 to 8.3) | (-13.1 to 6.4) | (-12.5 to 5.7) | (-11.4 to 4.7) | 13.9 | -0.2 (-1.2 to 0.8) |
| Delusions Subscale (DS) | 0-24 | 17 | 1.3 | TAU | (-3.3 to 6.0) | (-2.5 to 5.2) | (-2.2 to 4.9) | (-1.8 to 4.4) | (-1.5 to 4.2) | 5.8 | 0.2 (-0.6 to 1.0) |

*Effect estimate = iMAPS intervention+TAU - TAU*

*Standardised effect size (SES)=* *Effect estimate /* SD_pooled_; the corresponding 95%CI is calculated by dividing the limits of the 95%CI for the effect estimate by the SD_pooled_.

**Supplementary Table 5: Response rates as measured by the Positive and Negative Syndrome Scale (PANSS) by treatment allocated and time point.**

|  | **N (%)** | | | |
| --- | --- | --- | --- | --- |
|  | **16 Weeks** | | **28 Weeks** | |
|  | **iMAPs** | **TAU** | **iMAPs** | **TAU** |
| **Improvement category** | **n=25** | **n=11** | **n=18** | **n=8** |
| Deterioration or no change | 8 (32) | 5 (45) | 8 (44) | 2 (25) |
| >0% but <25% reduction from baseline | 7 (28) | 3 (27) | 4 (22) | 1 (13) |
| 25% to <50% reduction from baseline | 6 (24) | 3 (27) | 2 (11) | 1 (13) |
| 50% to <75% reduction from baseline | 2 (8) | 0 (0) | 1 (6) | 1 (13) |
| 75% to <100% reduction from baseline | 0 (0) | 0 (0) | 1 (6) | 0 (0) |
| Missing | 2 (8) | 0 (0) | 2 (11) | 3 (38) |

**Supplementary Table 6:** Number of Adverse Events and Serious Adverse Events by Treatment Group and Overall

|  | **iMAPS + TAU** | **TAU** | **Overall** |
| --- | --- | --- | --- |
| **Unrelated** |  |  |  |
| Total Serious Adverse Events (SAE), n  Hospital Admission  Physical  Mental Health/Psychiatric  Suicide Attempts | 1  1  0 | 0  0  0 | 2 |
| Total Adverse Events (AE), n  Suicidal Ideation with a plan | 8 | 3 | 11 |

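### SHEAP 7.2 names maximum likelihood but fixes neither variance divisor nor reference distribution; the usual likelihood-based treatment-effect intervals would under-cover at these sample sizes

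*Combined protocol and SAP*

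**What the plan says.** SHEAP 7.2 (Objective 4) analyses each candidate primary outcome "using a separate linear regression model at each time-point to estimate the effect sizes at 16 and 28 weeks". Each model "will include the fixed-effects for treatment therapy (iMAPS-2+TAU or TAU), care team type (CMHT or EI) and the corresponding baseline outcome score". With the intercept, that makes four mean parameters. The fitting method follows: "Models will be fitted using Maximum Likelihood Estimation (MLE"). The remaining continuous outcomes are analysed in the same way, with 95% intervals.

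SHEAP 5.1 states that "two-sided 100*(1-α)% confidence intervals with α ranging from 0.05 to 0.25 (in steps of 0.05) will be computed" for the proof-of-efficacy outcomes and that no p-values will be given. SHEAP 7.2 sets "a range of confidence intervals at different confidence levels (75%, 80%, 85%, 90% & 95"%) against the minimally important difference at 16 weeks: a standardised effect of 0.3 and, for PANSS total, also 5 points. At 28 weeks only the 95% level is planned.

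If normality is untenable, "bootstrap methods will be applied to estimate the confidence intervals of the treatment effects". The interval type, resampling scheme and number of replicates are not given. SHEAP 7.8 names Stata but no command.

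**The concern.** Fitting a normal linear model by maximum likelihood leaves the coefficients unchanged. It matters for the standard error and the multiplier. The maximum likelihood residual variance divides the residual sum of squares by n, not n−4, and likelihood inference is commonly paired with normal quantiles. With a few dozen participants both choices shorten the interval.

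The plan gives up testing and judges promise by where intervals at stated confidence levels fall relative to a threshold. Those readings help shortlist the primary outcome for the definitive trial (Objective 6). If the stated confidence is not the real confidence, that device is miscalibrated, and the plan's text does not prevent it.

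**Working it through.** **The plan's own figure.** The SHEAP gives no standard error, multiplier or coverage figure for the linear models. Its one precision figure is for retention: 45 participants give an exact binomial 95% interval no wider than 25% if retention is at least 80%. With 36/45 the exact interval is 65.4% to 90.4%, width 25.0%, and it narrows at higher retention. The figure reproduces and does not depend on how the regressions are fitted.

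**Inputs.**
- Mean parameters: 4 (SHEAP 7.2), so residual df = n−4.
- Planned n: "expected minimum 36 participants with outcome data" (SHEAP 4.4), so df = 32.
- Numbers by arm in Supplementary Table 5: 25+11 = 36 at 16 weeks and 18+8 = 26 at 28 weeks. Removing missing PANSS leaves 36−2 = 34 and 26−5 = 21.
- Levels: 95, 90, 85, 80 and 75% at 16 weeks; 95% at 28 weeks.

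**Formulas** (normal errors):
- ML standard error = least-squares standard error × √((n−4)/n).
- Width ratio, ML with z against least squares with t = √((n−4)/n) × z/t.
- True coverage, ML with z = P(|t on n−4 df| < z√((n−4)/n)).
- True coverage, z with unbiased variance = P(|t on n−4 df| < z).

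**Numbers in, n = 36.** √(32/36) = 0.943.
- 95%: z = 1.960, t = 2.037. Width ratio 0.943 × 1.960/2.037 = 0.907. Coverage P(|t32| < 1.848) = 92.6%.
- 75%: z = 1.150, t = 1.172. Width ratio 0.926. Coverage P(|t32| < 1.084) = 71.4%.

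All five levels at n = 36:

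| Nominal | Width ratio | Coverage, ML with z | Coverage, z with unbiased variance |
|---|---|---|---|
| 95% | 0.907 | 92.6% | 94.1% |
| 90% | 0.916 | 86.9% | 89.0% |
| 85% | 0.920 | 81.6% | 84.0% |
| 80% | 0.923 | 76.4% | 79.1% |
| 75% | 0.926 | 71.4% | 74.2% |

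With n = 34 (PANSS at 16 weeks) the 95% and 75% levels cover about 92.4% and 71.1%.

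**28 weeks, 95% only.**
- n = 26: √(22/26) = 0.920, t = 2.074, width ratio 0.869, coverage 91.5%.
- n = 21: √(17/21) = 0.900, t = 2.110, width ratio 0.836, coverage 90.4%.

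**Simulation check** (20,000 trials per setting). With arms of 25 and 11, ML with z covered 92.5% and 71.2% at the 95% and 75% levels. Least squares with t covered 94.9, 89.8, 84.7, 79.8 and 74.7% at the five levels. With arms of 18 and 8, ML with z covered 91.4% and least squares with t 95.1% at the 95% level.

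**On the PANSS scale, n = 36.** Baseline SD 10.7 (Supplementary Table 3). The documents give no baseline–outcome correlation, so 0.3 to 0.7 is assumed, with the baseline SD also used for the outcome. Least-squares standard error = 10.7 × √(1−r²) × √(1/25 + 1/11), which is 3.69 at r = 0.3 and 2.76 at r = 0.7. The 95% half-width is 5.1–6.8 points under ML with z and 5.6–7.5 under least squares with t. The 75% half-width is 3.0–4.0 against 3.2–4.3. The difference is about 0.5–0.7 points at 95% and 0.2–0.3 at 75%.

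**The case against.** The strongest reply is that the plan never mentions normal multipliers or a divisor of n. Naming maximum likelihood does not by itself determine the interval, and if the analyst uses the variance on n−4 df with t, there is no shortfall. That stands: the shortfall is conditional on the usual likelihood construction. But the plan names that method and says nothing to exclude its usual interval.

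A reader might infer that every interval in the trial is too narrow. The documents do not support this. Recruitment, adherence and retention use exact binomial intervals, harms (SHEAP 7.6) use differences in event rates, and the fallback is a bootstrap. Nor is a 75% interval planned at 28 weeks.

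A reader might also take Supplementary Table 4d (post hoc, N = 17) as proof that ML with z was used. It is not. That construction requires one standard error across the five levels. Those implied for the hallucinations subscale are 7.14, 7.11, 6.77, 7.10 and 7.00 under z, and 6.48, 6.61, 6.37, 6.74 and 6.69 under t on 13 df. For delusions they are 2.37, 2.34, 2.47, 2.42 and 2.48 under z, and 2.15, 2.17, 2.32, 2.30 and 2.37 under t. Neither multiplier gives a constant value within rounding (about ±0.03 to ±0.04). Separate bootstrap runs for each level could produce this, but that is conjecture.

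Finally, this is a feasibility trial. The progression criteria rest on recruitment, retention and adherence, and outcome shortlisting also draws on qualitative findings, sample-size feasibility and the steering committee. That limits the consequence; it does not justify mislabelled confidence levels.

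**Conclusion.** The point holds for the model-based treatment-effect intervals, and only if the usual likelihood-based construction is used. At the planned size the loss is then 2.4 percentage points at the 95% level (95 − 92.6) and 3.6 at the 75% level (75 − 71.4). At 28 weeks it is 3.5 points with 26 participants and 4.6 with 21. If only the multiplier is wrong, the loss at 95% with 36 participants is 0.9 points (95 − 94.1).

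The size is modest. It alters a judgement of promise only when an interval limit lies near a standardised effect of 0.3 or 5 PANSS points. The figures assume normal errors, four mean parameters and, for 36 and 26, that everyone counted at the visit is analysed. It is worth correcting because the intervals carry the efficacy reading and the remedy costs almost nothing.

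**What to change.** Replace the maximum likelihood sentence in SHEAP 7.2 with: ordinary least squares, residual variance on n−4 degrees of freedom, and t multipliers on the same degrees of freedom at all five levels and for the 95% intervals of the other continuous outcomes.

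For the bootstrap fallback, take all five levels from one set of replicates resampled within arm, and name the interval type (for example studentised or BCa) and the number of replicates.

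The cost is a sentence or two and no extra data; point estimates are unchanged. Compared with ML and z, intervals widen by 8% (75% level, 1/0.926) to 10% (95% level, 1/0.907) at n = 36. At 28 weeks the 95% interval widens by 15% at n = 26 (1/0.869) and 20% at n = 21 (1/0.836). If least squares with t was already intended, nothing changes except that the plan says so.
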